### Randomization and treatment contacts

Participants were randomly assigned to one of the four intervention groups using computer-generated permuted blocks of varying block sizes to ensure that the study groups would be proportionally balanced across study period and within each county and counselor. The randomization procedure was stratified on county and counselor. Study group proportions are listed in Table 1. We chose an unequal allocation to the four intervention groups, to end up with more participants with experience in the postpartum MI condition, in order to have adequate power to a test hypothesis about the combination of prenatal *and* postpartum MI versus postpartum-only MI. Overall, statistical power is adequate to detect MI versus HE differences in the primary outcomes. After participants gave consent and were enrolled, the County Counselor told the participant her prenatal study group assignment. The postpartum study group assignment was given at the 9-month postpartum visit.

**Table 1 T1:** Four-group design for the Baby Smiles study

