### Sample size

The sample size is 400 women with 80 to 120 women enrolled within any one county.

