### Analysis

Three *a priori* group contrasts will be used to test the primary hypotheses regarding intervention effects on the use of dental services (see Table 1 for a summary of the 4 study groups):

(1) Groups 1 and 2 (MI Prenatal) versus Groups 3 and 4 (HE Prenatal) will test the hypothesis that the MI intervention results in a greater frequency of utilization of dental care by the woman during pregnancy.

(2) Groups 1 and 3 (MI Postpartum) versus Groups 2 and 4 (HE Postpartum) tests the hypothesis that the MI intervention results in a greater frequency of utilization of preventive dental care by the children during the first 18 months of life.

(3) Group 1 (MI Prenatal and Postpartum) versus Group 3 (MI Postpartum only) will test the hypothesis combination of MI delivered during pregnancy and postpartum will result in a greater frequency of preventive dental care for children during the first 18 months of life.

A significance level of 0.016 was used in the sample size and power calculations for the primary hypotheses to take into account the three comparisons to be performed. The study will also provide some evidence for the effect of MI during pregnancy, without MI postpartum, on child utilization. However, the study is not powered to demonstrate this effect, which will likely be modest in the absence of intervention postpartum.

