### Primary outcome analysis

The analysis strategy for the primary hypotheses will involve intent-to-treat analyses, where women and their children will be compared according to their randomly- assigned intervention group regardless of whether, or how much of the intervention they actually received. The only exception to the intent-to-treat rule is in our analysis for child utilization of preventive dental care; this will be limited to only live-born children (*e*.*g*., miscarriages and stillborn will be excluded). Information about fetal loss will be collected by telephone interviews by the counselors with the participants because information about miscarriages is not on the state official birth record.

Intervention effects will be tested using the three *a priori* group contrasts described previously. Separate logistic regression analyses will be used to test each contrast using a significance level of 0.016.

A preliminary step in the analysis will be to check if the women in the four intervention groups are comparable on baseline values of prior dental utilization and important predictors of dental utilization (*e*.*g*. Readiness Ladder status, oral health quality of life). If an imbalance is found between the groups, additional covariates will be included in the logistic regression analyses to adjust for baseline differences. The primary independent variable in the regression analyses will be an indicator variable for intervention group. In addition, indicator variables for county and counselor will be included in all regression models to account for the stratification of the randomization by county and counselor.

Descriptive summaries will be produced for all the primary outcomes (mother and child dental utilization) by intervention group averaged over the four study counties, as well as by county, to assess the similarity of the observed intervention effects across the different counties. Formal testing for differences in the intervention effect among counties is possible by testing for interactions between county and intervention group in the regression analyses described below. However, we do not expect the intervention effects to differ vastly among the counties, and the sample size has not been selected to test for such county differences.

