The logistic regression models testing the primary hypotheses will be similar. They will differ in terms of the study groups to be compared and the corresponding dependent variable (i.e., mother’s or child’s receipt of dental services). In each model, the dependent variable is utilization of dental services and the primary independent variable is the study group. In addition, indicator variables for county and counselor will be included in the logistic regression to account for the stratified randomization by county and counselor. Additional analyses will also compare the intervention groups for other types (non-preventive) of dental care utilization.

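### The contrast 2 model omits the randomized prenatal assignment, although contrast 3 expects it to affect the same child outcome; the cost is a small loss of power

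*Protocol article*

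**What the plan says.** The Analysis section of the protocol article defines contrast 2 as "Groups 1 and 3 (MI Postpartum) versus Groups 2 and 4 (HE Postpartum"), so it pools over prenatal MI and prenatal HE. Contrast 3 compares Group 1 with Group 3 on the same outcome, preventive dental care for the child in the first 18 months. An effect of prenatal MI on that outcome is therefore a primary hypothesis.

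On the models, Primary outcome analysis states: "Separate logistic regression analyses will be used to test each contrast" and "The primary independent variable in the regression analyses will be an indicator variable for intervention group". It repeats that in each model "the primary independent variable is the study group". It puts county and counselor indicators in every model. Further covariates enter only if a baseline imbalance is found. Prenatal assignment is randomized and is not a baseline characteristic, so that route does not bring it in.

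Table 1 gives 148 and 148 women in the two prenatal arms under postpartum MI, and 52 and 52 under postpartum HE. The child analysis is limited to live births. Under Missing data, claims are unavailable only for women who explicitly refuse further participation. Participants learned their postpartum assignment at the 9-month visit.

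**The concern.** In a 2 × 2 factorial trial, a contrast on one factor is usually fitted with the other randomized factor in the model. Here the plan adjusts for the stratification factors but not for the second randomized factor, which it elsewhere expects to influence the child outcome. If prenatal MI works as contrast 3 supposes, the contrast 2 test gives up some power, and its odds ratio is averaged over two groups with different underlying rates. The stake is modest efficiency on one of three primary contrasts and clarity about which odds ratio is reported.

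**Working it through.** **The plan's own figures.** The cells sum to the stated total: 148 + 52 + 148 + 52 = 400 ("The sample size is 400 women with 80 to 120 women enrolled within any one county"). The per-contrast level of 0.016 is 0.05/3 = 0.01667 cut to three decimals, and 3 × 0.016 = 0.048. The article calls power adequate but gives no utilization rate, effect size or power figure, so its power calculation cannot be rebuilt.

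**Assumptions.** Two-sided alpha 0.016 (critical value 2.409); child use of 0.2 to 0.4 in Group 4 (HE at both stages); postpartum OR 2.2; prenatal OR 1 to 3; no interaction on the log-odds scale. County and counselor terms are left out of the calculation.

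**One case in full: Group 4 rate 0.3, prenatal OR 2.**

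- Rates: Group 4, 0.300; Group 3, 0.485; Group 2, 0.462; Group 1, 0.653.
- *Without the prenatal term.* The pooled rates are (0.653 + 0.485)/2 = 0.569 and (0.462 + 0.300)/2 = 0.381. The marginal OR is (0.569/0.431)/(0.381/0.619) = 2.15. SE = sqrt[1/(296 × 0.569 × 0.431) + 1/(104 × 0.381 × 0.619)] = 0.234. z = ln(2.15)/0.234 = 3.28. Power = Φ(3.28 − 2.409) = 80.8%.
- *With the prenatal term.* Cell weights np(1−p) are 33.5, 12.9, 37.0 and 10.9 for Groups 1 to 4. The information on the postpartum effect is 33.5 × 12.9/(33.5 + 12.9) + 37.0 × 10.9/(37.0 + 10.9) ≈ 17.75, so SE = 0.237. z = ln(2.20)/0.237 = 3.32. Power = Φ(3.32 − 2.409) = 82.0%.

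The SE rises slightly. Power rises because the estimate moves from 2.15 to 2.20.

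**Across the range.** Power without and with the term at a Group 4 rate of 0.3, and the gain over rates 0.2 to 0.4:

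| Prenatal OR | Without | With | Gain, rates 0.2–0.4 |
|---|---|---|---|
| 1.0 | 79.6% | 79.6% | 0 |
| 1.5 | 81.3% | 81.7% | about 0.4 points |
| 2.0 | 80.8% | 82.0% | 1.1–1.3 points |
| 3.0 | 77.7% | 80.7% | 2.8–3.3 points |

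**Simulation** (40,000 replicates, Group 4 rate 0.3, with 0%, 10% or 20% of women lost at random). Type I error without the term is 0.012 to 0.015 against a nominal 0.016; with the term it is 0.015 to 0.016. With 10% lost, power is 77.4% v 78.6% at prenatal OR 2, and 73.9% v 76.8% at OR 3.

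The conservatism has a simple source. The pooled model's variance includes the spread between prenatal arms, but the 1:1 split removes that spread from the comparison. At prenatal OR 3 under the null, the rates are 0.300 and 0.5625. The ratio of actual to model variance is [(0.210 + 0.246)/2]/(0.431 × 0.569) = 0.93. The true level is then 2[1 − Φ(2.409/sqrt(0.93))] ≈ 0.0125.

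**Exclusions.** Random loss of 5%, 10% or 20% leaves the prenatal share in the two postpartum arms within 0.026, 0.038 or 0.057 of each other in 95% of trials. Take analysed cells of 141, 44, 133 and 50 for Groups 1 to 4: the shares are 141/274 = 0.515 and 44/94 = 0.468, a gap of 0.047. With no true postpartum effect, the spurious OR is 1.02, 1.03 or 1.05 for prenatal OR 1.5, 2 or 3, a z shift of 0.08 to 0.21. A deliberately extreme gap of 0.11 gives 0.96 to 0.89.

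**Interaction on the risk-difference scale.** The 95% half-width is 1.96 × sqrt[p(1−p)(2/148 + 2/52)], which is 20.5 points at p = 0.3 and 22.3 at p = 0.5.

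**The case against.** The strongest reply is that this is a preference and not an error. Naming the primary independent variable does not list every term, a condensed article may leave the covariate list to the full protocol, and study group could mean a four-level factor that carries the prenatal assignment. Part of this stands: the text does not forbid the term. But the article does say which terms enter every model, and one indicator with a separate model per contrast is the more natural reading.

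Three stronger readings are tempting, and the documents do not support them.

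- *Omission wastes precision.* A reader might expect the standard error to fall when a prognostic factor is added, as in a linear model. In the planned logistic model it rises slightly; the gain is in power only.
- *Exclusions bias contrast 2.* Prenatal assignment is split 1:1 within each postpartum arm. Fetal loss comes before the postpartum assignment is disclosed and before that intervention starts. Loss that depends on the prenatal arm would therefore be alike in both postpartum arms apart from chance. Only refusals from about nine months on could differ by postpartum arm, and the article plans a sensitivity analysis for non-ignorable non-response.
- *Pooling is wrong unless there is no interaction.* With a 1:1 prenatal split in each arm, contrast 2 estimates a well-defined average postpartum effect. The planned summaries by intervention group, contrast 3, and the stated evidence on prenatal MI without postpartum MI already supply most of what a descriptive look at the interaction needs.

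**Conclusion.** The point holds as a minor, free improvement. The contrast 2 model as described leaves out a randomized factor that the plan expects to matter for the same outcome. The test remains valid and is slightly conservative. The power lost is about 0.4 to 1.3 points for a prenatal OR of 1.5 to 2, about 3 points for an OR of 3, and nothing if prenatal MI has no effect on child use. These figures rest on assumed rates, effect sizes and a two-sided test. The article states none of them; it says only that the prenatal effect without postpartum MI is likely modest, which makes the upper end of the range less likely. Distortion of contrast 2 through exclusions is limited to chance imbalance or late refusals, with a spurious OR of about 1.02 to 1.05 at a share gap of 0.047.

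**What to change.** In Primary outcome analysis, state that the contrast 2 logistic model, fitted in all live-born children, contains the prenatal assignment indicator alongside the postpartum, county and counselor indicators. The odds ratio is then conditional on prenatal assignment, so report a standardized (marginal) risk difference beside it. Optionally, give the prenatal-by-postpartum interaction with its interval, labeled descriptive only; at about ±20 to 22 points it cannot support a conclusion. The cost is one covariate and one or two reporting lines, with no new data and no change to the hypotheses, the sample size or the 0.016 level.

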#### Secondary aims

Data from the baseline questionnaire during pregnancy and the questionnaires at 3, 9 and 18 months postpartum will be used to describe and assess how the mother’s readiness to change and other factors, including depression, oral health knowledge, oral health quality of life, oral hygiene and dietary practices, and dental anxiety, a well as changes in these variables over the study period, mediate or moderate the effect of the MI. For example, it is hypothesized that MI, as compared to the HE materials, will result in a greater number of home oral health practices adopted by the mother to prevent dental caries in her young children during the first 18 months of life. To test this, the total number of home oral health practices by the mother as reported on the questionnaire at 18 months postpartum will be compared between mothers in the postpartum MI intervention (Groups 1 & 3) and mothers in the postpartum HE intervention (Groups 2 & 4) using linear regression analysis. Similarly, it is hypothesized that MI as compared to the HE will result in a greater percentage of mothers classified by the Readiness Ladder as in the action stage (versus pre-contemplation and contemplation stages), a greater increase in oral health knowledge and self-efficacy, and lower level of oral health fatalism. Logistic and linear regression analysis, similar to the analytical approach used to test the primary hypotheses, will be used to test the secondary hypotheses.

Additionally, it is hypothesized that outcomes will be mediated by a women’s readiness to change. We will test whether changes in readiness to change over the course of the intervention mediates the effects of MI on the outcome measures for the mother at three months post-partum and for the child by 18 months of age. First, the analyses for the primary hypotheses will be used to examine whether there is an effect of the MI intervention on mother’s outcomes at three months post-partum and child outcomes by 18 months of age. Second, to demonstrate the association between the intervention and readiness to change, we will construct regression models with readiness to change as the dependent variable (e.g., change between baseline and three months post-partum for the mother’s outcomes, and change between and/or three months postpartum and 9 or 18 postpartum for the child’s outcome) and intervention and the baseline value of readiness to change as independent variables. Third, to demonstrate the association between readiness to change and the outcome after adjusting for the intervention and to demonstrate the reduction of the intervention effect on the outcome after adjusting for readiness to change, we will construct regression models with both treatment and readiness to change as independent variables and the outcome measure as the dependent variable.

To formally test the mediation effect as described in the third step above, we will use a version of the Sobel test [41], which tests whether the indirect effect of intervention on the outcome through the mediator (defined as the product of the intervention to mediator path and the mediator to outcome path) is significantly different from zero. The mediation effect is referred to as the indirect effect of intervention because it reflects the intervention effect on the outcome through the mediating variable [42]. We will use the bootstrap method of Preacher and Hayes [43] to estimate the indirect effect and bias-corrected 95% confidence interval (CI) for each individual mediator and for all the mediators as a group, based on 1,000 bootstrap samples using a Statistical Package for the Social Sciences (SPSS®; SPSS Inc., Chicago, Illinois) macro (http://www.afhayes.com/spss-sas-and-mplus-macros-and-code.html).

Moderators of intervention outcomes are typically baseline characteristics that interact with the intervention to affect outcomes. Logistic and linear regression analyses will be performed to identify if baseline variables, such as depression, oral health knowledge, and dental anxiety, health fatalism, predict mother or child outcomes, and whether any of these variables moderate the intervention effect. The independent variable in these analyses will include an indicator for the intervention group contrast of interest, the baseline variable, and an interaction between the baseline variable and intervention group.

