**Methods/design:**

Baby Smiles was a five-year, four-site randomized intervention trial with a 2 × 2 factorial design. Four hundred participants were randomly assigned to one of four treatment arms in which they received either brief Motivational Interviewing (MI) or health education (HE) delivered during pregnancy and after the baby was born. In the prenatal study phase, the interventions were designed to encourage dental utilization during pregnancy. After childbirth, the focus was to utilize dental care for the infant by age one. The two primary outcome measures were dental utilization during pregnancy or up to two months postpartum for the mother, and preventive dental utilization by 18 months of age for the child. Medicaid claims data will be used to assess the primary outcomes. Questionnaires were administered at enrollment and 3, 9 and 18 months postpartum (study end) to assess mediating and moderating factors.

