### Missing data

Based on efforts to reduce attrition and missing data shown to be effective in our previous intervention work [20], and employed in this study, we expect to have an 80% retention rate of participation over the course of the study period. We will have even less missing data regarding dental utilization because we are able to obtain utilization data from the Medicaid database on all subjects, except those who explicitly refuse further participation in the study. In the case of non-ignorable non-response, a method based on augmented inverse probability of censoring weighted estimating equations will be used to perform a sensitivity analysis that examines how the estimated intervention effect on the primary outcome measure changes over a range of plausible values for the non-response mechanism [40].

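### The linear model for home oral health practices at 18 months prespecifies no pre-session value of the outcome, which gives up precision but not validity

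*Protocol article*

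**What the plan says.** All references are to the Protocol article.

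- **Endpoint and model (Secondary aims).** The total count of home practices "reported on the questionnaire at 18 months postpartum will be compared between mothers in the postpartum MI intervention" (Groups 1 and 3) and "mothers in the postpartum HE intervention (Groups 2 & 4) using linear regression analysis". No earlier value of the count is named as a covariate. Fatalism is framed in the same way, as a lower level under MI.
- **Covariates (Secondary aims; Primary outcome analysis).** The secondary tests use "Logistic and linear regression analysis, similar to the analytical approach used to test the primary hypotheses". In that approach, "indicator variables for county and counselor will be included in all regression models". Further covariates are added only if the groups are found to differ at baseline on prior dental utilization or its predictors.
- **Timing (Abstract; Study schedule; Randomization and treatment contacts).** "Questionnaires were administered at enrollment and 3, 9 and 18 months postpartum". The postpartum session is delivered, and the postpartum assignment disclosed, at 9 months.
- **Content of the questionnaires (Secondary aims).** Oral hygiene and dietary practices, and their changes over the study, are listed among the factors taken from the four questionnaires. The moderator paragraph treats oral health knowledge and health fatalism as baseline variables.
- **Missing data (Missing data).** "we expect to have an 80% retention rate of participation over the course of the study period", with less loss expected for the claims outcome. The planned sensitivity analysis examines "how the estimated intervention effect on the primary outcome measure changes over a range of plausible values". No method is named for questionnaire outcomes.

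**The concern.** For a repeatedly measured count or score, the mother's own earlier value is usually among the best predictors of the later one. Here it is left out of the fixed model, and the route by which other covariates enter does not lead to it. The imbalance check looks at baseline predictors of dental utilization, not at a postpartum practice count, and it makes adjustment depend on observed imbalance rather than on how prognostic the variable is. The article does state this kind of adjustment elsewhere: the readiness-to-change mediator models include the baseline value.

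Precision is at stake. The 296:104 split leaves the postpartum HE side small, and the expected 20% loss makes it smaller. The one non-response analysis that the article describes is aimed at the claims outcome, which it expects to be the more complete.

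**Working it through.** The article gives no effect size, SD or power for this endpoint, so there is no stated figure to reproduce.

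**Inputs from the article**
- Postpartum MI: 148 + 148 = 296. Postpartum HE: 52 + 52 = 104 (Table 1).
- Retention 80% (Missing data): 296 × 0.8 = 236.8 and 104 × 0.8 = 83.2, about 320 in all.

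**Assumptions, not in the article**
- Two-sided alpha 0.05 (the 0.016 level is stated for the primary hypotheses only), 80% power, equal retention in both arms.
- Correlation r between the pre-session and 18-month values: 0.3 to 0.7.

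**Unadjusted detectable difference, in SD units**
- Formula: (1.96 + 0.84) × sqrt(1/n1 + 1/n2).
- Full sample: sqrt(1/296 + 1/104) = 0.114, giving 0.319 SD.
- At 80% retention: sqrt(1/236.8 + 1/83.2) = 0.127, giving 0.357 SD.

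**Adjusted for an earlier value**

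The residual SD is multiplied by sqrt(1 − r²). The equivalent unadjusted sample is 320 / (1 − r²).

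| r | sqrt(1 − r²) | Detectable difference | Power for 0.30 SD | Equivalent N |
|---|---|---|---|---|
| 0 | 1 | 0.357 SD | 65.3% | 320 |
| 0.3 | 0.954 | 0.341 SD | 69.4% | 352 |
| 0.5 | 0.866 | 0.309 SD | 77.6% | 427 |
| 0.7 | 0.714 | 0.255 SD | 90.9% | 627 |

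The precision lost to 20% attrition is recovered when 1 − r² = 0.8, that is, at r = sqrt(0.2) = 0.45.

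**Validity**

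The postpartum factor was randomised, so the unadjusted contrast is unbiased apart from attrition. A value recorded before the session cannot have been changed by the session, so it is a legitimate covariate. Prenatal assignment does not confound the contrast either, because each prenatal arm splits 148:52 by postpartum arm.

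**Attrition, for scale only**

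With 20% missing, if non-responders in one arm differ from responders by an assumed 0.1 to 0.5 SD, the estimate shifts by 0.2 × 0.1 = 0.02 to 0.2 × 0.5 = 0.10 SD. With opposite departures in the two arms the shift doubles, to 0.04 to 0.20 SD.

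**The case against.** The strongest case against has four parts.

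1. **The earlier value may not exist in usable form.** The outcome concerns practices directed at the child. The article does not say that the identical count was taken before 18 months, or whether the 9-month form was completed before the 9-month session. This stands as a limit. At enrollment the child is not yet born, so that form may hold no such count, and an early postpartum count may correlate only weakly with the 18-month one. A 3-month form removes the doubt about order at the 9-month visit, but not the doubt about content.
2. **A reader might infer a completers-only analysis that leaves attrition unaddressed.** The article does not support that. It states no completers-only rule. A plain regression on the 18-month report would drop non-responders, but handling of missing secondary questionnaires may sit in the full protocol or analysis plan, neither of which is shown. Aiming a non-ignorable sensitivity analysis at the primary outcome is ordinary practice, and the article also mentions efforts to reduce attrition.
3. **Knowledge and self-efficacy are partly covered.** Those hypotheses are worded as a greater increase, which already implies use of an earlier value. This is right. For them only the form of the model remains to be fixed.
4. **The gain is assumed.** At r = 0.3 it is small, 0.357 to 0.341 SD. This is also right, but the adjustment costs almost nothing.

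The objection does not remove the central fact: the article fixes this model's endpoint, time point, groups and method, and makes any further adjustment depend on an imbalance check.

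**Conclusion.** The point holds as a minor one about efficiency in a secondary analysis. For home practices, and in the same way for fatalism, no pre-session value is prespecified, although the article indicates that such measures are collected repeatedly. Under the assumed alpha, power and equal retention, the detectable difference could fall from 0.357 SD to 0.341 SD (r = 0.3) or 0.309 SD (r = 0.5). The size rests on those correlations and on the measure having been asked before the session.

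A reader might conclude that the planned comparison is biased because the covariate is missing. It is not: randomisation protects the contrast, and the omission costs precision only. The narrow reach of the missing-data analysis is a reason for an optional extension, not an error in the plan.

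**What to change.** - **Main change.** In Secondary aims, state that the models for home practices and fatalism include, besides county and counselor, the latest value of the same measure recorded before the 9-month postpartum session, whatever the imbalance check shows. Use the 9-month form if it was completed before the session, otherwise the 3-month form, otherwise enrollment. State which form carries the item. If none does, say so and leave the model as it is.
- **Same form elsewhere.** Test the knowledge and self-efficacy hypotheses by ANCOVA, with the later value as outcome and the earlier value as covariate.
- **Missing earlier values.** Fix in advance how mothers without the earlier value are kept in the model, so that adjustment does not shrink the sample.
- **Optional.** Extend the sensitivity analysis in Missing data to the questionnaire outcomes, or impute them from earlier questionnaires and claims. Adjustment for prenatal assignment is also optional, since it is balanced by design.

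The cost is a few sentences and a little programming before the analysis. No new data are needed if the item was asked before the session.

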#### Secondary outcome variables

The two secondary outcome measures for the study will be 1) number of preventive home oral health practices taken by mothers to prevent caries in their young children, and 2) the mother’s readiness to change. The first outcome will be assessed by a questionnaire completed by the mother, or with assistance from the County Counselor [28,29]; the second outcome, readiness to change, will be assessed using a maternal-report “Readiness Ladder” modified for this study [30].

Additionally, several variables will be tested as mediators or moderators of the primary outcomes. These, also collected by the questionnaires, include prenatal depression [31], perceived stress [32,33], oral health impact [34], and dental anxiety [35]; and postpartum: dental anxiety [35], self-efficacy, oral health knowledge, fatalism [28,36], and child oral health impact [37].

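### Readiness to change, one of two named secondary outcomes, is tested as action stage yes/no although the mediation analysis models the same measure as change with a baseline value

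*Protocol article*

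**What the plan says.** Under Secondary outcome variables, the article lists two secondary outcome measures: a count of home oral health practices, and readiness to change. It adds that "readiness to change, will be assessed using a maternal-report “Readiness Ladder” modified for this study". It gives no number of rungs and no scoring rule.

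Under Secondary aims, the readiness hypothesis is stated as a "greater percentage of mothers classified by the Readiness Ladder as in the action stage (versus pre-contemplation and contemplation stages"). The method for this group of hypotheses is given as "Logistic and linear regression analysis, similar to the analytical approach used to test the primary hypotheses, will be used to test the secondary hypotheses". A percentage in one stage calls for the logistic model. The primary approach, under Primary outcome analysis, always includes county and counselor but adds baseline covariates only if an imbalance is found.

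Later in Secondary aims, step two of the mediation analysis uses "regression models with readiness to change as the dependent variable (e.g., change between baseline and three months post-partum for the mother’s outcomes". The predictors there are "intervention and the baseline value of readiness to change as independent variables".

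**The concern.** The three stages are ordered, and the test keeps only one of the two boundaries between them. A mother who moves from pre-contemplation to contemplation is scored the same as one who does not move. A mother already in the action stage at enrollment can only stay or fall back.

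Readiness is also the odd one out. In the same paragraph the other secondary variables keep their scale: a number of practices, an increase in knowledge and self-efficacy, a level of fatalism.

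The same question, whether MI changes readiness, is asked again in the mediation analysis with change as the dependent variable and the baseline value always in the model. At stake is power on a named secondary outcome. There is also a risk that the outcome test and the mediator model give different impressions of whether MI acted on its hypothesised mediator.

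**Working it through.** **Side by side.**
- Outcome test: yes/no at the action stage, logistic model, baseline readiness included only if an imbalance is found.
- Mediation step two: change between time points, baseline value always included. Change from a baseline value reads most naturally as an ordered or numeric coding. The three named stages already supply an order.

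**Inputs from the article.** Table 1 gives 148, 52, 148 and 52. Postpartum MI is 148 + 148 = 296 and postpartum HE is 52 + 52 = 104. At the 80% retention expected under Missing data, this is 0.8 × 296 ≈ 237 and 0.8 × 104 ≈ 83.

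**Not in the article, so assumed below.** The shape of the score, the number of rungs, the share of mothers in each stage, the effect size, the contrast, and two-sided alpha 0.05. (The stated 0.016 is for the primary hypotheses.) The article gives no figure for this outcome that could be reproduced.

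**Case A: a near-normal score, pure shift.** The efficiency of a cut with share p in action is φ(z_p)² / [p(1 − p)].
- p = 50%: 0.3989² / 0.25 = 0.637, loss 36.3%
- p = 30% or 70%: 0.576, loss 42.4%
- p = 20% or 80%: 0.2800² / 0.16 = 0.490, loss 51.0%
- p = 10% or 90%: 0.342, loss 65.8%

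**Case B: only the three named stages, proportional odds.** The efficiency of the cut against the three-category ordinal analysis is p(1 − p) / [(1 − Σp_i³)/3]. Shares are pre-contemplation / contemplation / action.
- 5/15/80: 0.16 / 0.1615 = 0.991, loss about 1%
- 20/30/50: 0.25 / 0.28 = 0.893, loss about 11%
- equal thirds: 0.2222 / 0.2963 = 0.75, loss 25%
- 40/40/20: 0.16 / 0.288 = 0.556, loss about 44%

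Three stages cut from a normal latent scale gave losses from about 6% to 35% in the cases tried, which lies inside this range.

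**Sensitivity to shape.** For an evenly used 10-rung ladder under proportional odds, (1 − 10 × 0.001)/3 = 0.33. The loss is 1 − 0.25/0.33 = 24% with half the mothers in action and 1 − 0.16/0.33 = 51.5% at 20% or 80%. The lower end of Case A therefore depends on the normal shape.

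**Illustrative power (Case A; 237 against 83; assumed shift 0.35 SD).** The standard error is √(1/237 + 1/83) = 0.1275, and power = Φ(0.35 × √efficiency / 0.1275 − 1.96).
- full score: Φ(0.78) = 78%
- cut with 50% in action: 59%
- cut with 70% in action: 55%
- cut with 80% in action: 48%

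A direct two-proportion calculation agrees in size. A shift of 0.357 SD, which has 80% power on the score, has 51%, 58%, 61% and 56% on the cut when 20%, 30%, 50% and 70% of HE mothers are in action.

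**The case against.** The strongest reply has four parts.

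1. **No score is documented.** The article never mentions a score or rungs. It speaks of Readiness Ladder status and of mothers being classified into stages. This stands. A reader might infer that a finely graded ladder score is on file and that the plan throws away a known 36-50% of it. The documents do not support that: the range in Case A needs a near-normal score, a pure shift and a particular share in action, and none of these is given. The power figures also rest on an assumed effect, alpha and contrast. What survives is that the stages themselves are ordered and that an ordinal analysis of them uses at least as much information.

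2. **The action stage is a meaningful boundary.** The interventions aim at dental visits, the Background describes movement toward action in a Stages of Change model, and the ladder's source and the full protocol are not at hand. This stands against any charge that the cut is arbitrary. It argues for reporting the percentage, not for resting the test on it alone.

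3. **The mediation analysis already models change, baseline-adjusted, and a percentage and a mean change are different quantities.** Both are true, so differing results would not be a contradiction in logic. But that model serves the mediation aim and is not the test of the secondary outcome. The article also does not state its coding. If change were taken on the same yes/no variable, the two analyses would match but the mediator would carry the same loss.

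4. **A ceiling affects any bounded ladder.** This is also true, and no baseline share is given. Adjusting for baseline readiness does not remove a ceiling, but it uses the information that is there.

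**Conclusion.** The point holds as a minor one. The article fixes the test of a named secondary outcome on a two-way split of an ordered measure, while its own mediation analysis treats that measure as change with a baseline value. The split ignores movement below the action stage and costs power.

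How much is lost is unknown from the article: about 36-51% of the information under a near-normal score with 20-80% of mothers in action (more outside that span), and about 1-44% against a three-category ordinal analysis if only the stages are recorded. With most mothers in action and few in the lowest stage, the loss could be negligible.

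The drop from 78% to between 48% and 59% power illustrates the mechanism and is not an estimate for this trial. No power claim is made for this outcome, and both primary outcomes come from Medicaid claims and are untouched.

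**What to change.** In Secondary aims, restate the readiness test on the ladder's ordered value: ordinal logistic regression on the three stages or, if rungs are recorded, linear or ordinal regression on the rungs. Adjust for baseline readiness, county and counselor. Use the same coding of readiness in step two of the mediation analysis and say so there. Keep the percentage of mothers in the action stage, by group, as a descriptive summary.

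The cost is a change of analysis wording; no new data are needed. The small downside is that the tested effect becomes a common odds ratio or a difference in rungs, which is less familiar than a percentage. The descriptive summary covers that.
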